## **I. Research Background and Current Status**

Acute pancreatitis (AP) is one of the common acute abdominal conditions in clinical practice, which may be associated with the failure of one or multiple organ functions. In high-income countries, the annual incidence rate is 34 cases per 100,000 person-years. The incidence of AP is on the rise worldwide, imposing a significant burden on healthcare and society. According to the revised Atlanta Classification of Pancreatitis in 2012, AP is categorized into three grades: mild acute pancreatitis (MAP), moderate severe acute pancreatitis (MSAP), and severe acute pancreatitis (SAP). These three types of pancreatitis have different clinical courses and outcomes. Most patients with MAP recover within one week, while those with SAP and MSAP have a more rapid disease progression, often accompanied by necrosis of peripancreatic tissues or (and) organ failure. The treatment is challenging, and the mortality rate is as high as 30%. Despite improvements in treatment and intensive care, SAP remains associated with high mortality. Therefore, early de-escalation of severity in SAP is crucial for reducing complications and improving prognosis.

The etiology of AP, such as secondary to gallstones (the most common cause), alcohol, endoscopic retrograde cholangiopancreatography (ERCP), and various drugs, leads to pathological cell pathways and organelle dysfunction, ultimately causing acinar cell death and triggering local and systemic inflammatory responses. The pathogenesis of AP has not been fully elucidated, and currently, the trypsinogen theory is dominant in the development of SAP. This theory posits that various etiologies lead to the activation of trypsinogen, which in turn activates a series of digestive enzymes, resulting in autodigestion and damage to the pancreas. A large number of proteolytic enzymes trigger local inflammation in the gland, and the pancreas continuously releases pro-inflammatory cytokines such as interleukin IL-1, IL-6, and IL-8, and TNF- $\alpha$ , inducing a systemic inflammatory state. This subsequently leads to strong activation of the sympathetic nervous system, causing a reduction in blood flow to the gastrointestinal system, which in turn leads to pancreatic ischemic necrosis, systemic inflammatory response syndrome (SIRS), multiple organ dysfunction syndrome (MODS), and acute respiratory distress syndrome (ARDS), pleural effusion, hypovolemia, renal failure, and even death. Although the mortality rate of acute pancreatitis has decreased in recent years due to improved diagnostic and nursing levels, the incidence and long-term sequelae remain a significant challenge for clinicians.

Persistent upper abdominal pain and pain radiating to the back are the earliest and most common symptoms of AP. Adequate pain management is crucial for SAP management. The pain in SAP patients can progress from an initial 1-3 days of persistent vague pain to severe abdominal pain lasting for several days or weeks. If pain is not

controlled in a timely and effective manner, it will affect the patient's comfort and recovery progress, and may even impact the patient's mood. The use of intravenous opioids for pain relief is associated with corresponding persistent side effects, such as respiratory depression, somnolence, delirium, myoclonus, nausea, vomiting, constipation, immune suppression, endocrine disorders, and addiction, among many other adverse reactions.

Thoracic epidural anesthesia (TEA) involves intermittent injection of low-concentration local anesthetics through a catheter into the epidural space, surrounding the connective tissue around the nerve roots, and blocking the regional nerve roots through local infiltration. It is a minimally invasive treatment method that reversibly controls the activity of sympathetic nerves within the region. TEA is a widely used anesthetic technique that can produce extensive visceral sympathetic and sensory nerve block effects, with roles in pain relief, anti-inflammation, and vasodilation to improve visceral organ perfusion. In addition to providing good anesthesia and analgesia, TEA also has many non-analgesic effects. Studies have shown that intraoperative and postoperative local application of anesthetics in the epidural space can prevent a reduction in visceral microvascular perfusion and shorten the recovery time of gastrointestinal function. In animal experiments conducted by Wang X et al., it was found that thoracic epidural anesthesia significantly promotes distal gastric microcirculatory perfusion and enhances the vitality of the stomach and intestines. Wang Huiying's research indicated that TEA can reduce the impact on gastrointestinal perfusion during endotoxemia while ensuring hemodynamic stability. It was also found that thoracic epidural anesthesia promotes gastric mucosal blood flow during sepsis. Paralytic ileus is a common complication of acute pancreatitis, and thoracic epidural anesthesia can improve paralytic ileus by blocking nociceptive afferent nerves and thoracolumbar sympathetic efferent fibers to maintain the function of parasympathetic efferent fibers. In addition to its analgesic effects, the regulatory role of TEA can also improve organ perfusion, delay intestinal acidosis in hypoxia, increase intramucosal pH in patients with peritonitis, thereby reducing postoperative complications, shortening hospital stay, and improving survival rates.

TEA is recommended as one of the early analgesic methods for acute pancreatitis due to its good analgesic effect and improvement of the prognosis of patients with acute pancreatitis. Although studies have shown benefits of TEA in acute pancreatitis in animals and humans, it has been clinically observed that some patients still experience unrelieved pain after continuous epidural infusion of analgesics (combination solution: 40 mg of nalbuphine, 225 mg of ropivacaine, 0.2 g of lidocaine, and 6 ml of 0.9% normal saline, totaling 50 ml), and require additional on-demand epidural combination solution (5 ml) to achieve effective pain relief. There is currently no definitive epidural analgesic regimen, lacking specificity and individualization, making it difficult to meet the unique needs of different patients. In the ICU setting, nurses, as the primary managers of patient pain, play a crucial role in pain

assessment, drug administration, and complication monitoring. However, the management plan for epidural drug administration in SAP patients still needs further optimization.

Therefore, this study, based on the Symptom Management Theory (SMT) and led by nurses, aims to objectively evaluate the effectiveness and safety of continuous epidural infusion compared with intermittent epidural combination solution (5 ml) on demand. The goal is to provide an optimized pain management plan for SAP patients. The research findings may offer potential clinical evidence for pancreatitis analgesic treatment and have significant implications for improving the prognosis of SAP.

This study is the first to explore the application of Symptom Management Theory (SMT) in pain management for patients with severe acute pancreatitis (SAP) led by nurses. Integrating SMT into pain management provides a structured approach for symptom assessment and intervention, which may enhance pain control. The study also introduces a flexible analgesic regimen, combining continuous thoracic epidural analgesia (TEA) with intermittent injections on demand, aiming to offer more personalized and effective pain management. These innovations may provide new insights for optimizing pain management plans for SAP patients and promote the role of nurses in pain management as well as the application of SMT in other clinical settings.

## **II. Research Introduction**

### **1. Research Title**

Effectiveness and Safety of Different Epidural Administration Methods Led by Nurses Based on Symptom Management Theory for Pain Management in Severe Acute Pancreatitis: A Clinical Study

### **3. Study Duration**

January 2025 to February 2026.

### **4. Research Center**

Department of Critical Care Medicine, Affiliated Hospital of Zunyi Medical University.

### **5. Research Purpose**

Given that animal experiments and clinical studies have shown additional benefits of thoracic epidural anesthesia

(TEA) for acute pancreatitis (AP), the efficacy of TEA in treating AP has garnered significant attention in recent years. The current expert consensus on analgesic treatment for severe acute pancreatitis (SAP) in China (2022 edition) also recommends the use of TEA for pain relief. However, clinical observations have revealed that some patients still experience unrelieved pain after continuous epidural infusion for analgesia and require additional on-demand drug injections to achieve significant pain reduction. Currently, there is no unified and clear protocol for epidural analgesia administration, which generally lacks specificity and individualization, making it difficult to fully meet the personalized needs of different patients. Particularly in the intensive care unit (ICU) setting, nurses, as the primary managers of patient pain, play a crucial role in pain assessment, drug administration, and complication monitoring. Therefore, there is an urgent need to develop and optimize more targeted and individualized management plans for epidural drug administration in SAP patients. This study aims to explore and compare the efficacy and safety of different epidural drug administration methods in pain management to provide an optimized pain management strategy for SAP patients.

## **6. Research Content**

This study was a single-center, randomized, controlled clinical trial protocol planned to include 76 patients with SAP who were randomly divided into two groups in order to assess the efficacy and safety of different SMT-based nurse-led epidural analgesia delivery modalities. In the control group, continuous TEA was used with a combination of nalbuphine 40 mg, ropivacaine 225 mg, lidocaine 0.2 g, and 0.9% saline 6 ml in a total of 50 ml, which was pumped at a rapid duration of 3-5 ml/h. When the patient's VAS-P exceeded 3 points or when the patient was unable to tolerate pain, the pumping of the combined solution was appropriately adjusted upward by 1-2 ml/h. In the experimental group, on the basis of continuous TEA, a pain management nurse led the TEA pain management strategy according to the SMT, reported to the doctor when the VAS-P exceeded 3 points or when the patient was unable to tolerate pain, and injected 5 ml of the combined drug solution intermittently with an intermittent interval time of greater than 2 hours each time, as per the doctor's prescription. Hours. The patient's pain response and feedback were also continuously monitored for timely adjustment of analgesic measures. The primary outcome indicator was VAS-P, and secondary outcome indicators included intra-abdominal pressure(IAP), number of additional interventions(NAI), dosage of combined drugs(DCD) , number of days of epidural placement(NDEP), and 16 adverse events(AE). Outcome indicators included puncture success rate(PSR), length of stay in ICU (ICU-LOS), 28-day mortality rate (28D-MR), and patient satisfaction score for analgesic effect(SAE).

## **7.Study Hypothesis**

(1) The experimental group will be superior to the control group in terms of VAS-P reduction and IAP control,

suggesting that intermittent epidural injections provide superior pain management and visceral protection.

(2) The incidence of adverse events in the experimental group will not be higher than that in the control group, and the length of hospitalization in the ICU and 28-day mortality will be lower, suggesting that the intermittent injection method is safe and may improve prognosis.

(3) Analgesic satisfaction scores will be higher in the experimental group than in the control group, suggesting that the nurse-led pain management program is more responsive to patient needs.

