## **8.Theory evidence**

Based on clinical practice, the team searches domestic and international databases to summarize the best evidence based on evidence-based, and develops pain management strategies based on the SMT theoretical framework. The theory focuses on managing patients' symptoms and consists of symptom experience, symptom management strategies and symptom outcomes. In the ICU, in response to pain in patients with SAP, SMT provides a structured approach to identifying pain symptoms by assessing pain levels on a regular basis using the VAS-P or patient self-report, recording scores, and thus understanding the patient's symptom experience. Based on these assessments, a 6W2H pain symptom management strategy was developed to individualize symptom management. The strategy consisted of two regimens of continuous epidural pumping of combination medications and on-demand intermittent epidural injections of 5 ml of combination medications on top of this. The key elements of why (purpose), who ( in charge), who (subject), where ( location), when ( timing), what ( measures), how ( methods), and how much ( frequency) were specified. Symptom outcome refers to the assessment of the effectiveness of the symptom management strategy after its implementation. In this study, the effectiveness of pain management was assessed primarily through indicators such as pain scores, dosage of combination medications, incidence of adverse events, length of stay in the ICU, mortality, and patient pain satisfaction. By recording and analyzing these indicators, the effectiveness and safety of different analgesic regimens were assessed to provide a scientific basis for optimizing pain management regimens. A comprehensive baseline assessment of other factors affecting pain, including person, environment and health/illness will be conducted to ensure consistent patient inclusion criteria. The SMT-based pain management framework for SAP patients is shown in [Figure 1](#).

[figure not shown]

Figure 1: Framework of Pain Management in SAP Patients Based on Symptom Management Theory (SMT)

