### **17.Study interventions**

Control group: Continuous TEA using a drug combination of: nalbuphine 40 mg + ropivacaine 225 mg + lidocaine 0.2 g + 0.9% saline 6 ml in a total volume of 50 ml at an infusion rate of 3-5 ml/h. When the patient's VAS-P exceeded a score of 3 or the pain was intolerable, upward adjustment of the pumped medication was made by 1-2 ml/h. and the number of additional interventions was recorded.

Experimental group : On the basis of continuous TEA, the pain management nurse led the TEA management strategy based on STM, and when the patient's VAS-P exceeded a score of 3 or pain was intolerable, an epidural injection of 5 ml of the combined drug solution was immediately administered, and the number of additional interventions was recorded. The duration of each interval was greater than 2 hours, and the patient's pain response and feedback were continuously monitored so that analgesic measures could be adjusted in a timely manner.

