## **28. Practical Significance:**

Despite the limitations, this study holds significant practical value. By exploring the potential benefits of nurse-led pain management based on SMT, it paves the way for providing more personalized and effective pain management strategies for SAP patients. If the experimental group shows superior outcomes, this could lead to a shift in clinical practice, favoring intermittent epidural injections over continuous TEA. This would not only enhance patient comfort and satisfaction but also potentially reduce healthcare costs associated with prolonged ICU stays and adverse events. The study results may also encourage further exploration of the role of nurses in pain management and the application of SMT in other clinical settings.

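### The protocol does not settle whether control patients also receive the nurse-led SMT programme, and on neither reading can the trial support every causal attribution in its three hypotheses

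*Protocol*

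**What the plan says.** **Arm descriptions.** Section 17 gives the control group continuous thoracic epidural analgesia (TEA). When VAS-P exceeds 3 or pain is intolerable, "upward adjustment of the pumped medication was made by 1-2 ml/h". For the experimental group it says "On the basis of continuous TEA, the pain management nurse led the TEA management strategy based on STM" (STM is evidently SMT), and at the same trigger "an epidural injection of 5 ml of the combined drug solution was immediately administered". It adds continuous monitoring of pain response and feedback, which the control text does not mention. Section 6 makes the same split.

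**Framing elsewhere.** The title speaks of "Different Epidural Administration Methods Led by Nurses Based on Symptom Management Theory", with methods in the plural. The aim in section I and the first sentence of section 6 likewise present the compared methods as nurse-led and SMT-based. Section 8 says "The strategy consisted of two regimens of continuous epidural pumping of combination medications and on-demand intermittent epidural injections". Section 9 gives the pain management nurses an SMT-based role for SAP patients without singling out an arm, and only step 4 of its five implementation steps differs by arm. Section 20 has these nurses giving the additional interventions in both groups.

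**Claims.** In section 7, hypothesis 1 reads the VAS-P and IAP difference as "suggesting that intermittent epidural injections provide superior pain management and visceral protection". Hypothesis 2 credits safety and prognosis to the injection method. Hypothesis 3 reads the satisfaction difference as "suggesting that the nurse-led pain management program is more responsive to patient needs". Section 28 says that superior experimental results could shift practice, "favoring intermittent epidural injections over continuous TEA".

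**The concern.** Taken literally, sections 6 and 17 make the arms differ in two things at once: the nurse-led SMT programme with its feedback monitoring, and the response to pain above the threshold (injection or rate increase). Section 7 then assigns some outcomes to one component and one outcome to the other. A single two-arm contrast cannot do that.

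The matter is more than wording, because the primary outcome is a mark the patient makes on a line (section 19) and satisfaction is a patient rating from 0 to 10 (section 22). Section 14 concedes that patient blinding cannot be fully secured. Blinded data collectors do not help when the patient is the rater. If one arm gets more structured attention, lower pain scores and higher satisfaction could follow without any effect of the injection.

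Staff could also deliver control care in either of two ways and still be following some part of the protocol. Care that has been given cannot be redefined afterwards.

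**Working it through.** **The plan's own figure.** Section 12 sizes one two-arm VAS-P contrast: δ = 2, σ = 2.5, two-sided α = 0.05, power 90%. With σ² as a multiplier, n = 2(1.960 + 1.282)² × 2.5² / 2² = 32.84, so 33 per group. Then 66 × 1.15 = 75.9, so 76 in total. The stated figures reproduce. They power the overall difference between arms and nothing finer.

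**Set-up.** Let S be the effect of the nurse-led SMT programme and B the effect of responding with an injection instead of a rate increase. Continuous TEA is present in both arms (sections 6 and 17; section 20 also counts additional interventions after continuous TEA in both groups). There are three unknowns: the control-level mean, S and B. Two arms supply two means.

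| | SMT in experimental arm only (sections 6 and 17, arm texts) | SMT in both arms (title, section I, opening of 6, sections 8, 9, 20) |
|---|---|---|
| Design row, control (intercept, S, B) | 1, 0, 0 | 1, 1, 0 |
| Design row, experimental | 1, 1, 1 | 1, 1, 1 |
| Rank of design matrix | 2 of 3 | 2 of 3 |
| Experimental minus control | S + B | B |
| Hypotheses 1 and 2, credited to injections | package effect only | testable as injection versus rate adjustment |
| Hypothesis 3, credited to nurse-led programme | package effect only | no contrast; S is the same in both arms |
| Section 28, injections over continuous TEA | no contrast | no contrast |

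**What this means at the planned effect.** Under the first reading, an observed difference equal to δ = 2 fits S = 0 and B = 2, S = 2 and B = 0, or S = 1 and B = 1 equally well. These values illustrate non-identification and estimate nothing. Under the second reading the 2 points would be B, and the data say nothing about S.

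**Section 28.** The column for continuous TEA is 1 in both rows, identical to the intercept. No patient described in sections 6 and 17 receives injections without continuous TEA, so injections in place of continuous TEA is not a comparison the trial makes. The aim in section I, which sets continuous infusion against on-demand injection, has the same looseness, as does step 4 of section 9, which lists only injection for the experimental arm.

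**The case against.** The strongest reply is that SMT is the common framework and the delivery method is the only intended contrast. The title, section I, the opening of section 6 and sections 8, 9 and 20 support this. Sections 6 and 17 never say that control patients are denied SMT-based care, and figures that are not shown may set out its content by arm. This stands in part: a reader might infer that control patients definitely go without the programme, and the protocol does not establish that. It contradicts itself. But the reply does not rescue section 7 as a whole, because shared SMT care removes the contrast that hypothesis 3 relies on.

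A reader might also infer that the trial cannot answer its questions at all. That goes too far. Section 5 sets out to compare administration methods, and randomisation gives a valid comparison of the regimens as delivered. The comparative half of each hypothesis is estimable; only the clauses on what a difference suggests are affected.

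Nor does the protocol plan a formal conclusion against continuous TEA. Section 28 discusses practical significance, is worded conditionally, and may use continuous TEA as shorthand for the control arm. It needs rewording, but it is not a defective analysis rule.

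Finally, the attention argument concerns self-rated outcomes. IAP is read from a bladder manometer (section 20), and nothing in the protocol suggests that attention alone would change it.

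**Conclusion.** The point holds as an internal contradiction with consequences for interpretation, and it should be fixed. The definition of control-arm care is inconsistent, and no reading supports every attribution in section 7. With SMT in one arm, none of the three hypotheses can credit a single component, and the VAS-P and satisfaction contrasts are open to bias from unequal attention. With SMT in both arms, hypotheses 1 and 2 stand as injection versus rate adjustment, and the nurse-led clause of hypothesis 3 fails. On either reading, section 28's comparison with continuous TEA, and any claim that the trial by itself shows the benefit of nurse-led SMT care, have no contrast behind them.

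In size, one of three unknowns is unidentified whichever reading is taken. The overall difference between regimens and its sample size are unaffected. The amount of any attention bias cannot be derived from the protocol. The conclusion assumes that the arm contents are as the text of sections 6 and 17 gives them, apart from the SMT question itself.

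**What to change.** 1. Reconcile the arm descriptions in sections 6 and 17 with the title, section I, the opening of section 6 and sections 8, 9 and 20, so that one definition of control-arm care is stated throughout.
2. Preferably, specify the same SMT-based assessment, monitoring and feedback in both arms, as most sections already imply. The response to VAS-P above 3 or intolerable pain is then the only difference. Keep hypotheses 1 and 2 as statements about that difference, and delete the nurse-led attribution from hypothesis 3.
3. If SMT stays in the experimental arm only, reword hypotheses 1, 2 and 3 to claim the combined package alone, and acknowledge the possible effect of unequal attention on patient-rated outcomes.
4. In either case, describe the comparison in section 28 and the aim in section I as on-demand injection added to continuous TEA versus rate adjustment of continuous TEA. Drop the claim that the trial shows the benefit of nurse-led SMT care by itself.

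The cost is protocol wording and, under option 2, a training instruction. The nurses already act in both groups, and no patients are added. The trial gives up a separate claim for nurse-led SMT care, which its design cannot support. For scale only: separating the two effects would take a third arm, 3 × 33 = 99 evaluable patients at the protocol's own group size. With 15% dropout, 33 / 0.85 = 38.8, so 39 per arm and 117 in total, before any adjustment for multiple comparisons. That is not proposed here.

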## 12. Sample size

This study is a randomized controlled trial, and the primary outcome indicator is the VAS-P score. From the literature review, it is known that the mean VAS-P scores after the intervention of similar control group protocols are 1-3, and there is no study similar to the experimental group, and the mean VAS-P scores of the pre-experimental group are 1-2. It is proposed to formulate the standard deviation of the two groups combined  $\sigma = 2.5$ , and it is expected that the pain symptom scores of the experimental group can be decreased by  $\delta = 2$ . Setting a bilaterality of  $\alpha = 0.05$ , the degree of certainty is 90%, and based on the formula of the sample size [Formula 1](#), the sample size is calculated for each group of  $N = 33$  participants. Assuming a 15% dropout rate, a total of 76 participants were needed based on a 1:1 randomization ratio.

*Formula 1:*

$$n = \frac{2(z_{\alpha} + z_{\beta})^2 + \sigma^2}{\delta^2}$$

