## 14. Blinding

Because this is an interventional study, pain management nurses will not be aware of the specific grouping of patients until after they begin to implement the intervention, but they will not be involved in other parts of the study. Although there are measures that can be taken to try to keep patients blinded to subgroups, there are still difficulties in avoiding exposure altogether. For this reason, data collectors and data analysts will remain blinded to the specific intervention protocols, and independent persons who are not aware of the specific intervention protocols will be responsible for data collection and analysis, thus ensuring that data collectors and statistical

analysts are blinded to the treatment assignment and minimizing potential bias in data processing and analysis.

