## **21.Adverse Events**

Puncture-related AE : Healthcare workers observe and record the following 8 indicators during daily care and examination: spinal cord and nerve root injury, epidural hematoma, puncture site infection, total spinal anesthesia, headache after dural puncture, intradural infection, catheter blockage, catheter breakage and ectasia. The number of cases of AE was counted for the period of epidural placement.

Drug-related AE: Pain management nurses observed and recorded the following 8 indicators after the patient's medication: anaphylaxis, hypotension, nausea/vomiting, itching, tremor, sensory disturbances in the lower limbs, fever, decreased oxygen saturation, bradycardia or tachycardia. The statistical methods and times were the same as those for puncture-related AE.

22.Outcome Indicators

Puncture surgery rate (PSR): Calculate the ratio of the number of successful puncture cases to the total number of punctures, which was counted by the data collector.

Length of stay in ICU (ICU-LOS): when patients are transferred out of ICU, the total number of days of ICU stay is recorded.

28-day mortality rate (28D-MR): count the number of patients who died within 28 days and calculate the 28-day mortality rate.

Satisfaction with analgesic effect (SAE): patients' satisfaction with the analgesic effect was assessed using a 0-10 scale, with 0 indicating very dissatisfied and 10 indicating very satisfied. It was collected by the data collector on the day of epidural tube removal.The intervention and data collection process are shown in [Figure 4](#).

[figure not shown]

Figure 5: Intervention and Data Collection Process

23. Quality control

(1) All staff must undergo standardized training and pass assessments to ensure consistent implementation of the intervention, minimizing both executor and assessor bias.

(2) Collected data will be cross-verified by two researchers before being entered into the system to ensure data accuracy.

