#### **24.Data analysis**

Data will be analyzed in this study using GraphPad Prism software to ensure accuracy and consistency of results. For baseline characteristics data, patients' age, gender, admission time, and disease-related clinical information will be descriptive statistics, Categorical variables will be presented as frequencies and proportions, whereas normally distributed continuous variables will be described using means and standard deviations. For non-normally distributed data, descriptive statistics will utilize median and percentile values (P25 and P75). Between-group comparisons will be carried out using t-tests, analysis of variance, chi-square tests, Mann-Whitney U tests, and statistical methods for repeated measures data to assess differences among the groups. The significance level in this study will be set at  $\alpha=0.05$ , with  $P<0.05$  indicating statistical significance.

The changes in the primary outcome indicator VAS-P at different time points (0h, 1h, 6h, 12h, 24h, 48h, 72h) will be assessed by repeated measures analysis of variance (ANOVA) if the data conform to a normal distribution. Secondary outcome indicators, such as intra-abdominal pressure (IAP), will be analyzed in the same manner. The number of additional interventions (NAI) and the dose of coadministered medication (DCD) will be expressed as mean  $\pm$  SD or median (IQR), and comparisons between groups will be made using the t-test or the Mann-Whitney test. The number of days of epidural placement (NDEP) will also be subjected to descriptive statistics and between-group comparisons. The number of cases of adverse events (AE) will be expressed as frequency, and comparisons between groups will be made using the chi-square test or Fisher's exact test. The outcome indicators, including puncture success rate (PSR), length of stay in the ICU (ICU-LOS), 28-day mortality rate (28D-MR), and satisfaction with analgesic effect score (SAE), will be subjected to descriptive statistics and between-group comparisons using the chi-square test or Fisher's exact test, as well as the t-test or the Mann-Whitney test.

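### The hypothesis that adverse events will not be more frequent in the experimental group is paired only with a test of difference, and a non-significant result from that test cannot support it

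*Protocol*

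**What the plan says.** Section 7, Hypothesis (2), states "The incidence of adverse events in the experimental group will not be higher than that in the control group". Together with lower ICU stay and 28-day mortality, this is taken as "suggesting that the intermittent injection method is safe and may improve prognosis".

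Section 24 gives the analysis: "The number of cases of adverse events (AE) will be expressed as frequency, and comparisons between groups will be made using the chi-square test", with Fisher's exact test as the alternative. The same section applies one significance level, 0.05, to the whole study. It gives no separate rule for safety, no margin and no interval for the difference in incidence.

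Section 12 derives the 76 participants from VAS-P only. No adverse-event rate is assumed anywhere in the protocol.

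On recording, Section 21 says of drug-related events: "Pain management nurses observed and recorded the following 8 indicators" after medication. Section 14 says of the same nurses, who learn the allocation once they start the intervention, "but they will not be involved in other parts of the study". Section 9 has the nurses record adverse reactions and also makes the data collection researcher responsible for collecting adverse events. Section 21 counts events over the whole period of epidural placement.

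**The concern.** A claim that incidence is not higher is a claim about an upper bound: any excess is smaller than some amount that matters. A chi-square or Fisher test asks a different question, whether the data are compatible with no difference. In a small trial they are often compatible with no difference and, equally, with a substantial excess. The protocol fixes both the hypothesis and the test, and the two do not fit.

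Safety is half of the study title, and Section 28 foresees a shift in practice if the experimental arm does better. If the only adverse-event result is a P value above 0.05, the natural way to report on Hypothesis (2) is to say that it was met, although the data may leave a doubling of risk open.

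There is a smaller, related question. It is unclear whose record feeds the comparison: that of the nurses who give the injections and know the arm, or that of the blinded collectors.

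**Working it through.** **1. The plan's own sample size.** Inputs from Section 12: SD 2.5, difference 2, two-sided alpha 0.05, power 90%. The standard formula gives

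n = 2(1.960 + 1.282)² × 2.5² / 2² = 32.8, so 33 per arm.

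33 × 1.15 = 37.95, so 38 per arm and 76 in total. The stated figures are reproduced, using the product form of the formula. Adverse events do not enter. The numbers available for the safety comparison are therefore 38 per arm (randomised) or 33 per arm (the number before the dropout allowance).

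**2. Chance that the planned test detects a true doubling.** All event rates here are assumptions. For each pair of true rates, every possible pair of event counts was weighted by its binomial probability, and the pairs with two-sided P<0.05 were summed. Chi-square is without continuity correction.

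| Assumed rates (control vs experimental) | 38 per arm: Fisher | 38 per arm: chi-square | 33 per arm: Fisher | 33 per arm: chi-square |
|---|---|---|---|---|
| 10% vs 20% | 14.9% | 23.5% | 11.5% | 21% |
| 20% vs 40% | 39.7% | 48.9% | 32.4% | 44% |

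For 10% vs 20%, the chance of a non-significant result runs from 100 − 23.5 = 76.5% to 100 − 11.5 = 88.5%, that is, roughly 77% to 88%. For 20% vs 40% it runs from 100 − 48.9 = 51.1% to 100 − 32.4 = 67.6%.

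**3. What an interval would show.** With equal rates p and n = 38 per arm, the half-width of the 95% CI for the risk difference is 1.96 × √(2p(1−p)/38).

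- p = 0.10: 1.96 × √(0.18/38) = 0.135, about ±13 points.
- p = 0.20: 1.96 × √(0.32/38) = 0.180, about ±18 points.

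Even identical observed counts leave a sizeable excess open. The Newcombe 95% upper limit is 15 points for 4 vs 4 events in 38, and 18 points for 8 vs 8.

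**4. What a margin would require.** The protocol gives none, so 10 points is used as an illustration, with equal true rates and one-sided 0.025. Power is Φ(0.10/√(2p(1−p)/n) − 1.96).

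| Assumed rate in both arms | Power, 38 per arm | Power, 33 per arm | n per arm for 80% power |
|---|---|---|---|
| 10% | 31% | 27% | 142 |
| 20% | 19% | 17% | 252 |
| 30% | 16% | 14% | 330 |

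At 38 per arm, 80% power is reached only with a low rate and a wide margin, for example 5% with 15 points (85%) or 10% with 20 points (83%).

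**5. Who records.** Sections 9 and 21 have the pain management nurses record drug reactions. Section 14 keeps them out of everything beyond the intervention. Section 9 also assigns the collection of adverse events to the data collection researcher. Read together, these do not say which record is compared, or whether it is made without knowledge of the arm.

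**The case against.** Four points can be made for the plan.

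- **Wording.** A reader might infer that the protocol will declare safety proved whenever P exceeds 0.05. It does not say so. Hypothesis (2) is an expectation, and its conclusion is softened to a suggestion. Reading a non-significant result as support is an inference, drawn because no other criterion is given. This limits how strongly the point may be put, but it does not remove the mismatch.
- **Size.** A reader might infer that any doubling of risk would almost certainly be missed. That fails at higher rates: at 20% vs 40% with 38 per arm, the test detects the excess in 40% to 49% of trials. Quoting Fisher alone would also be one-sided, since Section 24 allows chi-square, which has more power.
- **Safeguards.** Section 27 concedes that the sample may miss small but clinically relevant differences, and Section 33 sets up a data safety monitoring committee that reviews adverse events. Interval reporting is often left to a statistical analysis plan, which is not at hand. These points are fair, but none supplies a criterion for the hypothesis as worded, and a doubling of risk need not be a small difference.
- **Recording.** A reader might infer that the adverse-event comparison is biased by open recording. The documents show only an unresolved tension. Noting reactions after a dose can be read as part of delivering the intervention, Section 9 gives the collector a role, and several listed events (hypotension, fever, oxygen saturation, heart rate) are measured signs. What stands is the need to reconcile the sections.

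**Conclusion.** The point holds as a mismatch between hypothesis and test. Hypothesis (2) needs a bound on the excess; Section 24 offers only a test of difference, in a trial sized for pain. A non-significant result would not support the hypothesis. Under assumed rates of 10% and 20%, it would be expected in roughly 77% to 88% of trials despite a true doubling. At 20% and 40% the figure is about 51% to 68%. These sizes rest on assumed event rates and on 33 to 38 patients per arm. The mismatch itself does not depend on them. The primary VAS-P comparison is unaffected. The question of who records drug-related events is secondary: an inconsistency to resolve, not a demonstrated bias.

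**What to change.** **Preferred.** Restate the adverse-event part of Hypothesis (2) as descriptive. In Section 24, report the number of patients with at least one event per arm, with the risk difference and its 95% CI. State that P>0.05 will not be read as evidence of safety.

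**Alternative.** If the claim that incidence is not higher is kept, require the upper 95% limit of the risk difference to lie below a margin stated and justified now. Acknowledge that power is low at this size: 31% or less for a 10-point margin at rates of 10% to 30%.

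**Secondary.** Reconcile Sections 9, 14 and 21 on who records the drug-related events used in the comparison. If the blinded collectors also ask about events when they collect VAS-P, that record should supplement the nurses' record, not replace it. The visits stop at 72 h and on-demand injections fall between them, whereas events are counted over the whole placement period. A visit-only record could miss brief or late events.

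**Cost.** Wording and one interval calculation, with no extra patients. The price is a weaker but correct safety statement.
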